#### Population-level tertiary endpoints

Tertiary endpoints include the incidence of VT, NVT, all IPD, and non-pneumococcal invasive bacterial disease which will be analysed using the same methods as in the ‘Population-level incidence endpoints’ section. The endpoint of NVT prevalence in children with clinical pneumonia will be analysed at the population level using the same methods as for the primary endpoint.

#### Presentation of results

The results of non-inferiority analyses will be summarised in a figure showing the point estimates and confidence intervals for multiple endpoints in relation to vertical reference lines indicating the null effect and the non-inferiority margin. The figure will only include endpoints with sufficient statistical power to test the non-inferiority hypothesis.

#### Adjustment for covariates

As noted earlier, the stratifying covariates used in randomisation: location in BHDSS or FWHDSS and high-low cluster baseline incidence will be included in all statistical models. The other variables used to generate restricted randomisation lists to ensure balance in baseline characteristics will not be included in analyses [27]. Age will be included in models to estimate schedule impact on community-level VT carriage (via age stratification) and VT carriage in young infants (age in days). If differential case ascertainment or access to care is evident, we will consider further adjusted analyses.

#### Effect modification

We have a priori interest to examine the following potential effect modifiers for the primary endpoint: (a) age (2–12 weeks, 13 weeks to 9 months, 10–23 months, and 24–59 months) and (b) inpatient/outpatient status. The number of cases of each endpoint in these subgroups may not be sufficient to assess non-inferiority. We will examine the strength of evidence for differences between subgroups using interaction tests.

#### Assumptions to be checked for statistical methods

For regression models using GEE, we assume that observations within the same cluster may be correlated. We will use the common assumption in cluster-randomised trials that the correlation matrix is exchangeable, meaning that observations on individuals in different clusters are uncorrelated and that observations on individuals in the same cluster all have the same correlation coefficient. This assumption is usually correct for individuals living in the same community. The GEE method does not require a distributional assumption for cluster-level values.

Inference based on analyses of incidence using cluster-level summaries assumes a normal distribution of the observed cluster summaries [21]. We will inspect the distribution of the observed cluster summaries for skewness. If the cluster summaries in the incidence analyses are positively skewed, we will consider applying a logarithmic transformation to the incidence rates [21].

#### Alternative methods if distributional assumptions do not hold

If GEE regression analyses using the log link function for binary data do not converge, we will implement GEE regression analyses using a logit link functions. Prevalence ratios will be obtained following marginal standardisation and confidence intervals using the delta method.

#### Sensitivity analyses

No sensitivity analyses are planned.

#### Sub-group analyses

Analysis of the primary endpoint will be conducted in the subgroups specified in the ‘effect modification section’. We will also examine the relative schedule impact on VT carriage in the community, by survey age-strata, i.e. 0–11 months, 12–23 months, 2–4 years, 5–9 years, 10–14 years, 15–44 years, and ≥45 years.

### Missing data

Missing data will be reported in tables and figures. Specific missing data will include NP pneumococcal carriage and serotype for resident children with clinical pneumonia, NP carriage in the community surveys, blood culture and chest X-ray results for hospitalised patients with suspected pneumonia, sepsis, or meningitis, and group allocation. We do not expect missingness for these variables to be greater than 2–3%. If the percentage of missing data is greater than 10% for any of the specified variables, we will consider methods to impute missing values and sensitivity analyses with imputed data.

### Additional analyses

Analysis of the primary endpoint using data from year 2 of intervention (1 Nov 2020–31 Oct 2021) will be conducted with a superiority hypothesis, aiming to detect potential early effects of the interventions. The statistical model will estimate the prevalence difference (and 95% CI). Interpretation will be based on the a priori statement that the smallest significant difference is prevalence ratio of 1.47.

Analysis will include group-wise calculation of the intra-cluster correlation coefficients for VT pneumococcal carriage in children with clinical pneumonia, population-based carriage survey in year 4, and the survey of carriage in young infants in year 4.

We will explore potential differential risk of events in the alternative schedule group before and after administration of the booster dose. We will calculate incidence rate ratios for radiological pneumonia and hypoxic pneumonia among those who received PCV per-protocol (see the ‘Definition and assessment of adherence to the intervention’ section). We will count events from 14 days after administration of the first dose of PCV, before administration of the second dose (alternative schedule group), and ≤288 days of age (9 months and 2 weeks). We will also count events from 7 days after administration of the second dose of PCV (alternative schedule group) and >288 days of age. These analyses will isolate the period of potential inferiority before the booster dose in the alternative schedule group.

*Safety*

PCV13 is a licensed product with an excellent safety profile. Safety at the individual level is best evaluated by comparison of infants enrolled at EPI clinics to receive the trial intervention schedules. In these safety analyses, the effects of the two schedules will not be diluted by the inclusion of children who may not have been enrolled to receive the interventions, as is done in population-level analyses. Thus, any differences between the two schedules will be more likely detected in these individual-level analyses. Individual-level ITT and PP safety analyses will include the endpoints of VT IPD, radiological pneumonia, and mortality incidence (see the ‘Individual-level cohort incidence endpoints’ section).

Serious adverse events (SAE), which will primarily be events of hospitalisation and deaths at home detected by the HDSS, will be reported in each group at the population-level (residents aged 0–260 weeks) and individual-level in infants enrolled to receive the interventions. Events of radiological pneumonia and VT IPD will be deemed SAEs of special interest, and reported in each group at the individual-level in enrolled infants.

Unsolicited reactogenicity events within 7 days of a dose of PCV recorded at EPI clinics will be reported in each group [5]. Severe adverse reactions to doses of PCV will be reported for each group, specifically episodes of anaphylaxis and severe local reactions. The probability of suspected unexpected severe adverse reactions (SUSAR) to doses of PCV will be reported based on the probability of any SAE in the 3 days following administration of dose two (age 10 weeks) or dose three (age 14 weeks) of PCV in the standard schedule group compared to 3-day period following these age points in the alternative schedule group. Similarly, we will compare the probability of an SAE in the 3 days following administration of the booster dose at age 9 months in the alternative schedule group compared to the 3-day period following this age point in the standard schedule group. These probabilities will be compared to indicate signals of potential SUSARs related to PCV.

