### Adherence and protocol deviations

#### Definition and assessment of adherence to the intervention

##### Vaccination status—per-protocol

Vaccination per-protocol (PP) will be defined as a child enrolled into the study at ≤273 days (≤40 weeks) of age and who received the allocated schedule of PCV doses during follow-up. PP administration of the standard schedule of three doses will require allocation to the standard schedule and administration of three doses of PCV at ≤152 days (≤22 weeks) of age. PP administration of the alternative schedule will require administration of two doses of PCV, the first dose ≤152 days (≤22 weeks) of age, and administration of the second dose ≥273 days (≥40 weeks) and ≤365 days (≤52 weeks) of age.

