##### Vaccination status—incomplete vaccination

Incomplete vaccination with the standard schedule will be defined as administration of only one dose of PCV, or administration of two doses of PCV with the second dose administered at ≤252 days (≤36 weeks) of age. Incomplete vaccination with the alternative schedule will be defined as the administration of only one dose of PCV, at any age. For individual-level ITT analyses, children with incomplete vaccination will be assigned to the group to which they were randomised.

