##### Vaccination status—out-migration or death before age to complete vaccination

Vaccination status in individual-level analyses will be defined as out-migration or death before age to complete if the child migrates out at an age before which their PCV schedule could reasonably be completed. Infants resident in standard schedule villages who out-migrate or die before age ≤112 days (16 weeks) and receive zero doses of PCV will be classified as ‘standard schedule, out-migration/death, unvaccinated before age 16 weeks’ and ‘standard schedule, out-migration/death, incomplete before age 16 weeks’ if one or two doses are received. Infants resident in alternative schedule villages who out-migrate or die before age ≤294 days (≤42 weeks) and receive zero doses of PCV will be classified as ‘alternative schedule, out-migration/death, unvaccinated before age 42 weeks’ and ‘alternative schedule, out-migration/death, complete before age 42 weeks’ if one dose of PCV is received.

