##### Assessment of individual-level adherence

Individual-level adherence will be assessed as (a) PP vaccination, (b) ITT vaccination, (c) incomplete vaccination, (d) cross-over, (e) unvaccinated, or (f) migration/death before completion. Individual-level adherence will be assessed cumulatively over the 4 years of intervention and reported as proportions of participants enrolled at EPI clinics who fall into these mutually exclusive categories.

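### The pre-booster comparison keeps only alternative-arm children who later get the booster, so after dose 3 events that lead to death, departure or a missed booster drop out of that arm only

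*SAP article*

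**What the plan says.** The SAP's Additional analyses section plans an exploratory comparison of the periods before and after the booster, for two outcomes and in one population: "We will calculate incidence rate ratios for radiological pneumonia and hypoxic pneumonia among those who received PCV per-protocol". The first window is defined as follows: "We will count events from 14 days after administration of the first dose of PCV, before administration of the second dose (alternative schedule group"; it closes at 288 days of age. The stated aim is: "These analyses will isolate the period of potential inferiority before the booster dose in the alternative schedule group".

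The section refers back to the adherence definitions for the meaning of per-protocol. There the two arms differ:

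- Standard schedule: "administration of three doses of PCV at ≤152 days (≤22 weeks) of age".
- Alternative schedule: a first dose by day 152 and then "administration of the second dose ≥273 days (≥40 weeks) and ≤365 days (≤52 weeks) of age".

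Children without the booster have their own categories. For one dose only: "Incomplete vaccination with the alternative schedule will be defined as the administration of only one dose of PCV, at any age". For early exit, a separate class covers "Infants resident in alternative schedule villages who out-migrate or die before age ≤294 days (≤42 weeks"); the corresponding standard-arm limit is 112 days. Under Assessment of individual-level adherence, the classes are "reported as proportions of participants enrolled at EPI clinics who fall into these mutually exclusive categories". A child in one of these classes therefore cannot also be per-protocol. No ITT version of the booster split is described.

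**The concern.** A comparison of the time before the booster should include children on facts known when that time begins. Here, entry in the alternative arm depends on a dose given at or after the end of the window. A child whose illness ends in death, departure or a missed booster is taken out of the analysis together with that illness.

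In the standard arm the deciding dose comes much earlier. Take hypoxic pneumonia at day 200 that proves fatal. In a standard-arm child with three doses by day 152, the event is counted. In an alternative-arm child it is not, because that child can never receive a second dose at day 273 or later.

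At stake is whether this analysis can do what it is planned for. Removal caused by the event itself can only lower the alternative-arm rate, so it works against finding the excess that the window is meant to reveal.

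**Working it through.** The SAP gives no expected ratio or power for this analysis, so there is no figure of its own to reproduce. Two things can be worked out: how much of each arm's window depends on a later dose, and what that does to the rate ratio under stated assumptions.

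**1. Time that depends on a later dose**

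Inputs from the SAP: dose 1 scheduled at 6 weeks (42 days); start 14 days after dose 1; end at day 288, or at dose 2 in the alternative arm; alternative-arm dose 2 at day 273 to 365; standard-arm dose 3 at 14 weeks (98 days) on schedule, day 152 at the latest.

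- Start: 42 + 14 = day 56.
- Standard-arm window: 288 − 56 = 232 days.
- Alternative-arm window: 273 − 56 = 217 days, up to 232 days if dose 2 falls after day 288. All of it depends on the later booster.
- Standard-arm time that depends on dose 3: 98 − 56 = 42 days (42/232 = 18%), up to 152 − 56 = 96 days (96/232 = 41%).
- Standard-arm time that depends on no later dose: 190 days (82%) down to 136 days (59%).

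If dose 1 is given at 70 days, the 10-week case mentioned under Assessment of population-level adherence, the window is 288 − 84 = 204 days. Of this, 42 days (dose 3 at day 126) to 68 days (dose 3 at day 152) depend on dose 3.

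Both arms therefore depend on later doses before dose 3. Only the alternative arm does so between dose 3 and day 288.

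**2. Effect on the rate ratio**

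Let f be the share of window events that are fatal, and s the share of the standard-arm window after dose 3. Assume that events are spread evenly and are rare, so that lost person-time can be ignored. The alternative arm keeps 1 − f of its events. The standard arm loses f only in the part before dose 3, so it keeps 1 − f(1 − s). The true ratio is multiplied by

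(1 − f) / (1 − f(1 − s)).

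| f (assumed) | s = 0.819 | s = 0.586 |
|---|---|---|
| 0 | 1.00 | 1.00 |
| 0.02 | 0.984 | 0.988 |
| 0.05 | 0.959 | 0.970 |
| 0.10 | 0.917 | 0.939 |

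**3. Check by simulation**

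First events were simulated for 2 million children per arm with a true ratio of 1.0. All of these inputs are assumptions: 0.05 events per child-year, dose 1 at 42 to 70 days, background exit hazard 0.0001 per day, and 10% dose-missing unrelated to illness in both arms. Each arm's per-protocol rule was then applied.

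- No link between event and later dosing or survival: 1.01, which is no bias beyond simulation noise.
- Death the only link, case fatality 2%, 5% and 10%: 0.98, 0.96 and 0.93.
- No later dose required in either arm: 0.995 to 1.005 in every scenario.

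The simulated values lie within the range given by the formula. As an example, a true ratio of 1.5 would read as 1.5 × 0.98 = 1.47 down to 1.5 × 0.93 = 1.40.

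**The case against.** **Per-protocol is a deliberate choice.** The SAP uses it for biological effect and for comparison between sites. That is a sound reason for requiring doses already due. Before the booster, however, a one-dose alternative-arm child has received everything the schedule asks for so far. Requiring the booster adds no purity to that window and only selects on the future.

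**The label used for early exits.** The SAP describes one-dose alternative-arm children who die or leave by day 294 with the word complete, which might suggest that they count as per-protocol. They do not: the per-protocol definition requires two doses, and the categories are mutually exclusive.

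**The harm is visible elsewhere.** This largely stands. ITT radiological pneumonia is counted from enrolment, ITT hypoxic pneumonia and mortality are planned, and the adherence categories are reported by arm. None of these is split at the booster, so none answers this particular question.

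**The bias may be small.** This also stands. The booster window is 365 − 273 = 92 days wide and outreach clinics visit monthly, so a child who recovers has about three chances to be boosted on time, and that child's event is kept.

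A reader might infer more than the documents support:

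- *That all comparable standard-arm events stay in.* This is true only after dose 3. Before it, a standard-arm child who dies, leaves or falls behind is removed as well.
- *That the bias is large.* Adding 5 to 10 percentage points of extra dose-missing after an event to the same simulation gives 0.84 to 0.95, but nothing in the SAP supports those values.
- *That missed doses for unrelated reasons add a further bias of known range.* Such removal occurs in both arms, and the SAP has no figures from which to derive a net effect.

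**Conclusion.** The point holds for one exploratory analysis. The alternative-arm pre-booster rate is computed only in children who survived, stayed and were later boosted, whereas the standard-arm rate after dose 3 carries no such condition. Event-driven removal favours the alternative schedule.

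The size is unknown from the SAP. It is nil if events affect neither later dosing nor survival. It is a factor of about 0.93 to 0.98 if 2 to 10% of events are fatal and death is the only link; those percentages are assumptions.

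It would go too far to infer that the trial's main results or its safety evidence as a whole are compromised. The primary endpoint does not use the per-protocol cohort, and the secondary radiological pneumonia endpoint is ITT from enrolment. The improvement is worthwhile because it is cheap, not because the trial depends on it.

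**What to change.** In Additional analyses, add a version of the pre-booster window, for the same two outcomes, that does not require the booster:

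- **Who:** enrolled children by allocated group, with dose 1 at ≤152 days of age and no later dose required in either arm.
- **Start:** the later of enrolment and 14 days after dose 1.
- **End:** the earliest of dose 2 (alternative arm), 288 days of age, death and out-migration.
- **Enrolment age:** restrict to children enrolled at ≤182 days in both arms. Under Eligibility, from 22 August 2019 to 7 February 2020 the standard arm stopped enrolling at that age while alternative villages enrolled up to 9 months, and late enrolment in one arm only would distort the comparison.

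Show the planned per-protocol version beside it, and leave the post-booster window as it is.

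The work is a change of wording and one more run of a planned model on data already collected. The statistical cost is dilution: standard-arm children with only one or two doses come in and pull the ratio toward 1. If 10% of standard-arm follow-up were effectively one-dose (assumed), a true 1.5 would read 1.5/(0.9 + 0.1 × 1.5) = 1.43; at 20%, 1.5/(0.8 + 0.2 × 1.5) = 1.36. For comparison, the formula for the per-protocol version at f = 0.10 gives 1.5 × 0.917 = 1.38 to 1.5 × 0.939 = 1.41. The dilution could therefore match the bias removed if many children are under-dosed. Neither version is sufficient alone, and the two should be read together.

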The setting is a rural African location where over 75% of vaccination is provided through outreach visiting villages only once per month. The age at vaccination may therefore be different from that which applies in urban African settings, where vaccination may be more frequently available. The conduct of the trial has enhanced service delivery for the primary series of doses by a marginal degree so the age at vaccination in the trial is largely representative of the situation that would pertain should the alternative schedule be introduced in the routine EPI. However, the timing and coverage of the PCV booster dose at 9 months of age may have been enhanced to some degree. Thus, ITT analysis using the individual-level cohort will show the impact of the alternative schedule under a particular set of vaccination delivery circumstances that may not represent a routine setting. Analysis in the population-level population most clearly defines the conditions needed to combine all direct and indirect effects of the schedules in the population. The individual-level cohort PP results can most easily be compared between different study sites. The trial will include mathematical modelling of schedule effects on VT carriage with varied coverage of the alternative schedule PCV booster dose. Table 1 presents the analysis framework, specifying the populations and cohorts, observations and follow-up, endpoints, and effect measures.

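### The pre-/post-booster analysis caps the pre-booster window at day 288 although the per-protocol booster may come as late as day 365, so the latest single-dose time in the alternative group falls in neither window

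*SAP article*

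**What the plan says.** All of this is in the SAP article. Under Additional analyses, the plan will compare radiological and hypoxic pneumonia before and after the booster "among those who received PCV per-protocol".

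- **First window.** It opens 14 days after dose 1 ("We will count events from 14 days after administration of the first dose of PCV"). Its end is given by two conditions joined by 'and': "before administration of the second dose (alternative schedule group), and ≤288 days of age (9 months and 2 weeks").
- **Second window.** "We will also count events from 7 days after administration of the second dose of PCV (alternative schedule group) and >288 days of age".
- **Stated purpose.** "These analyses will isolate the period of potential inferiority before the booster dose in the alternative schedule group".

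Under Vaccination status—per-protocol, the alternative schedule requires "administration of the second dose ≥273 days (≥40 weeks) and ≤365 days (≤52 weeks) of age". Under Background and rationale, the setting is one where "over 75% of vaccination is provided through outreach visiting villages only once per month".

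**The concern.** The window limits and the per-protocol booster range do not fit together. The first window closes at a fixed age of 288 days, but a child in this analysis set may properly remain unboosted for up to 11 weeks after that. The second window cannot open for such a child until 7 days after dose 2. The time in between belongs to neither window, and it is the part of the single-dose period furthest from dose 1. Standard-group children have no such gap: they pass from the first window to the second between day 288 and day 289.

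This is the only analysis in the SAP with a window confined to the time before the booster, and it concerns disease endpoints that bear on safety. If the rule drops part of that time in one group and leaves the two groups with different age coverage, the rate ratios do not describe quite what the plan says they describe.

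**Working it through.** **Inputs.** Booster day B: 273 to 365 (per-protocol definition). First-window end, second-window start and the 7-day lag: Additional analyses. I take person-time to follow the same windows as the events.

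**The plan's own figure.** Nine months and two weeks: 9 × 365.25/12 + 14 = 287.9, which rounds to 288 days. The cut-off reproduces.

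**Assigning each day of age d in the alternative group**

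- First window: d < B and d ≤ 288.
- Second window: d ≥ B + 7 and d > 288.
- Unboosted days in neither window: max(0, B − 289).

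| Booster day B | Unboosted days in neither window | All days in neither window | Ages affected |
|---|---|---|---|
| 273 | 0 | 16 | 273–288 |
| 281 | 0 | 8 | 281–288 |
| 289 | 0 | 7 | 289–295 |
| 290 | 1 | 8 | 289–296 |
| 303 | 14 | 21 | 289–309 |
| 336 | 47 | 54 | 289–342 |
| 365 | 76 | 83 | 289–371 |

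The third column includes the 7-day lag after dose 2, which the plan leaves out on purpose. Early boosters have a smaller gap of another kind: for B from 273 to 287, the time from dose 2 to day 288 is in neither window. At B = 273 that is 16 days, of which 7 are the lag and 9 are not.

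**Share of all pre-booster time dropped.** The documents give no booster-age distribution and no distribution of age at dose 1, so both are assumed here. With dose 1 on day 42 the pre-booster period opens on day 56, which is 273 − 56 = 217 days before day 273. With dose 1 on day 70 it opens on day 84, which is 273 − 84 = 189 days before. Age is treated as continuous, so the loss for a booster on day B is B − 288 if positive.

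- *All boosted within 30 days, uniform over 273–303.* Mean loss 15²/(2 × 30) = 3.75 days. Mean unboosted time after day 273 is 15 days. Share: 3.75/(217 + 15) = 1.6%, or 3.75/(189 + 15) = 1.8%.
- *30% miss one clinic (70% over 273–303, 30% over 303–333).* Mean loss 0.7 × 3.75 + 0.3 × 30 = 11.6 days. Mean unboosted time after day 273 is 0.7 × 15 + 0.3 × 45 = 24 days. Share: 11.6/241 = 4.8%, or 11.6/213 = 5.4%.
- *Uniform over the whole range 273–365.* Mean loss 77²/(2 × 92) = 32.2 days. Mean unboosted time after day 273 is 46 days. Share: 32.2/263 = 12.2%, or 32.2/235 = 13.7%.

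Counting whole days gives slightly smaller mean losses in the first and third cases (3.0 and 31.5 days). For one child boosted on day 365, the loss is 76 of 309 pre-booster days (25%) with dose 1 on day 42, and 76 of 281 (27%) with dose 1 on day 70.

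**The other reading.** Suppose the bracketed mention of the alternative group means that the dose limit applies to that group and the age limit to the standard group. No unboosted time is then lost. But the first window runs to as late as day 364 in the alternative group and stops at day 288 in the standard group. The second opens between days 280 and 372 in one group and on day 289 in the other.

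**The case against.** The best defence is that a common age ceiling keeps the groups comparable, that everything counted as pre-booster is truly unboosted, and that a rate uses person-time, so shortening the window does not by itself bias it. The absence of contamination stands. The comparability does not fully stand: children boosted on days 273–287 leave the first window before standard-group children do, and the second window starts at different ages in the two groups. In the first window this mismatch is small, at most days 273–288 against some 200 shared days.

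The stakes are also limited, and this stands in full. The plan presents the analysis as exploratory. Events in the gap are still counted in the ITT analysis from enrolment and in the PP incidence analysis from 14 days after dose 1. An excess would lose its attribution to a window; it would not vanish.

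A reader might infer more than the text supports:

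- *That illness which delays the booster hides in the gap.* An event that pushes the booster past day 288 must occur by day 288, when the child is still in the first window, and it is counted there.
- *That a quarter to 70% of the unboosted time is lost.* Under the three assumed timings, such shares (25%, 48% and 70%) arise only if the denominator is restricted to unboosted time after day 273.
- *That late boosters are known to be common.* Monthly outreach makes boosters after day 288 likely, but the SAP gives no distribution and says that booster timing may have been enhanced to some degree by the trial.

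**Conclusion.** The point holds on the text, as a fault of truncation and unequal age coverage in an exploratory analysis. Read as written, the rule leaves up to 76 unboosted days per child in neither window, in the alternative group only. On the other reading, the groups are compared over different ages. Either way the windows do not deliver the stated purpose, and the two passages need to be reconciled.

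The size is modest: about 2%, 5% or 12–14% of all pre-booster time under the three assumed timings, with dose 1 assumed at day 42 to 70. The first needs prompt boosting and the last is an extreme spread.

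It would be tempting to conclude that the rule conceals harm from the single-dose period. The documents do not support that, because the direction of any bias is uncertain. If protection wanes after one dose, dropping the latest unboosted time would understate an excess. If incidence falls with age, removing alternative-group time at days 273–288 would tilt the first ratio slightly upwards, and starting that group's second window later would tilt the second downwards. The primary endpoint and the overall ITT and PP incidence results are unaffected.

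**What to change.** Define the windows by the actual date of dose 2 and drop the fixed day-288 cut:

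- In the alternative group, run the pre-booster window from 14 days after dose 1 to the day before dose 2, and start the post-booster window 7 days after dose 2. Exclude the 7-day lag from both windows or show it separately.
- Split person-time and events in both groups into the same age bands, for example ≤273, 274–365 and >365 days.
- Estimate the pre-booster and post-booster rate ratios each against standard-group time in the same bands, with age band in the model.

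With these bands, pre-booster time falls in the first two and post-booster time in the last two. Standard-group time in the middle band then serves as comparator for both. This changes only how time is counted in the analysis, not when any dose is given.

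The cost is SAP wording and a person-time split on dates already held. The downside is one extra age term and a less simple table in an analysis with few events. Some age difference will remain within the middle band, where pre-booster time is younger than post-booster time.

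### The SUSAR signal comparison starts its 3-day window at the actual dose in one arm and at a nominal age in the other, so the two windows are not comparable

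*SAP article*

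**What the plan says.** The Safety text under Additional analyses in the SAP article sets out two between-arm comparisons of any serious adverse event (SAE).

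- Doses two and three: the standard arm is observed from the day each dose is actually given, with 10 and 14 weeks shown only as the scheduled ages. The undosed arm is tied to those ages themselves: "compared to 3-day period following these age points in the alternative schedule group".
- Booster: here the alternative arm is the dosed one, observed for "the 3 days following administration of the booster dose at age 9 months in the alternative schedule group". The undosed standard arm is again tied to the nominal age, with no visit or dose needed to open its window.

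The purpose is stated: "These probabilities will be compared to indicate signals of potential SUSARs related to PCV". The events counted are described at the start of the SAE text: "Serious adverse events (SAE), which will primarily be events of hospitalisation and deaths at home detected by the HDSS".

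Elsewhere the SAP describes when doses are actually given. Background and rationale says that "over 75% of vaccination is provided through outreach visiting villages only once per month". Assessment of population-level adherence notes that a dose due at 6 weeks may first be obtainable at 10 weeks. The per-protocol definition requires "administration of three doses of PCV at ≤152 days (≤22 weeks) of age" in the standard arm and a booster between 273 and 365 days in the alternative arm. The Safety text describes no matching on actual age at dosing, no age adjustment and no attendance condition for the undosed arm.

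**The concern.** The two sides of each comparison run on different clocks. On the dosed side, time zero is a clinic visit at which the child was alive, present and vaccinated. On the undosed side it is a birthday-type date that every child reaches, whatever the child's state of health.

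Two things follow. First, the dosed window opens later in life than the nominal age whenever the clinic visit is late, so background risk is taken at different ages. Second, only the dosed side is selected on attending and being vaccinated that day. Since the event is mainly hospital admission, acute illness around the index day matters directly. Randomisation of clusters does not protect the comparison, because the selection happens after allocation and in one arm only. At stake is whether a SUSAR signal check can be read at face value, particularly when it shows no excess.

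**Working it through.** The SAP gives no rate, sample size or power for this comparison, so there is no stated figure to reproduce. The check has three parts.

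**1. How far the clocks can differ (SAP age limits)**

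- Dose three: nominal age 14 × 7 = 98 days; per-protocol limit 152 days. Gap: 152 − 98 = 54 days.
- Dose two: nominal age 10 × 7 = 70 days. Dose three must also fall by day 152. If the schedule's own 4-week spacing is kept, dose two falls by 152 − 28 = 124 days, a gap of 124 − 70 = 54 days.
- Booster: per-protocol window 273 to 365 days. Gap: 365 − 273 = 92 days.

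The comparison is not restricted to per-protocol doses, so these limits indicate the spread and do not bound it.

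**2. How often the windows would coincide (assumption: a clinic every 28 days, delay uniform over 0 to 27 days)**

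- Mean delay: (0 + 1 + … + 27) / 28 = 13.5 days.
- Two 3-day windows overlap only if the delay is 0, 1 or 2 days: 3/28 = 11% of dosed children.

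**3. What the mismatch could do to the ratio**

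Observed ratio = true ratio × h × a. Here h is the effect of selection on attendance, and a is background SAE risk at the actual dose age divided by that at the nominal age. The SAP gives neither, so both are assumptions.

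Selection alone (a = 1), true ratio 2.0:

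| h | Observed ratio | True ratio that would appear as 1.0 (1/h) |
|---|---|---|
| 1.0 | 2.0 | 1.00 |
| 0.7 | 1.4 | 1.43 |
| 0.5 | 1.0 | 2.00 |
| 0.3 | 0.6 | 3.33 |

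Age alone (h = 1), true ratio 2.0: with a = 0.8 the observed ratio is 2.0 × 0.8 = 1.6. With risk rising by the same factor, a = 1/0.8 = 1.25, it is 2.0 × 1.25 = 2.5. The age component therefore has no fixed direction.

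**The case against.** The strongest reply is that this is one descriptive signal check for a licensed vaccine, with no test, margin or decision rule attached. Unsolicited reactions within 7 days of a dose, anaphylaxis, severe local reactions and overall SAEs by arm are all reported separately, mortality is analysed in the enrolled cohort, and the DMC regularly views the accruing data. None of these relies on the nominal-age anchor. This stands, and it limits the importance of the point. It does not repair the comparison: the separate outputs do not give a between-arm contrast of any SAE in the 3 days around dosing, which is what this analysis adds.

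It can also be said that the age points might mean the ages at which doses were really given. The only ages printed are 10 weeks, 14 weeks and 9 months. If actual ages were meant, the SAP does not say how an undosed child is assigned one, so the wording would still need to be settled.

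Some stronger readings are tempting and are not supported:

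- A reader might infer that age and selection both bias towards reassurance. Without SAE rates by age, only the selection effect has an expected direction, and even that is inference, because the SAP gives no rule on vaccinating unwell infants.
- A reader might infer that dose two can fall 12 weeks late (22 − 10). That overlooks that all three doses must be given by day 152.
- A reader might infer that the undosed side includes children who never attend a clinic. The same Safety section favours comparing infants enrolled at EPI clinics, who have attended at least once.
- A reader might infer that children already in hospital at the age point raise the comparator risk. Their admission precedes the window, and they cannot readily have a new one within it. The masking argument rests on children falling ill around the age point.

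**Conclusion.** The point holds as a defect in a stated rule, not as missing detail. The dosed window is anchored on administration and the undosed window on a nominal age, in both comparisons, and the SAP's own account of monthly outreach and wide dose-age limits shows that these will often differ. Nothing else in the document aligns them.

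The size of the resulting bias is unknown. The range of 0.6 to 2.0 for a true ratio of 2.0 depends wholly on an assumed selection factor of 0.3 to 1.0, whose upper end is no bias at all. What can be said firmly is that the ratio as defined mixes a reaction effect with a selection effect that could mask it and an age effect of unknown direction. A null result would therefore give weak reassurance. The analysis should be corrected, but it is supportive and does not touch the primary or secondary endpoints.

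**What to change.** Use the same anchor in both arms. Give each enrolled comparator child an index date drawn from the actual age-at-dose distribution of the dosed arm, within the same randomisation stratum and calendar period. Apply one condition to both arms: alive, resident and not in hospital on the index date. Do this for doses two and three and, with the arms exchanged, for the booster.

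This aligns age but removes attendance selection only in part, since a child can be unwell without being in hospital. As a supportive check, add a within-child comparison of the 3 days after the actual dose with a later post-dose window, its length fixed in advance and ending before any further dose. That removes stable differences between children. A short-lived dip in risk just after a clinic visit could still remain, so the two analyses should be read together.

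The cost is revised SAP wording and modest extra programming. Vaccines received, residence and hospital admissions are already recorded, so no new data collection is evident, and no dose or clinical rule changes.
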